## Abstract

**Background:**

Continuous loss of muscle mass and strength are the consequences of the ageing process, which increase the risk of falls among older people. Falls can lead to severe consequences such as bone fractures and hampered physical and psychological well-being. Regular exercise is the key to reversing muscle atrophy and relieving sarcopenia. However, the frailty of older people and the recent COVID-19 pandemic may affect their confidence to leave home to attend classes in the community. A feasible and effective alternative should be explored.

**Methods:**

The primary objective is to evaluate the effectiveness of tele-exercise (TE) in relation to physical functioning and exercise adherence among community-dwelling older people at risk of falls in comparison with a community-based group (CB). The secondary objective includes evaluating older people’s experience with tele-exercise, emphasizing their psychological welfare, social well-being, and acceptance of the telehealth approach. The design, conduct, and report follow the SPIRIT guidelines (Standard Protocol Items: recommended items to address in a Clinical Trial Protocol and Related Documents). Older people will be recruited from 10 local community centres in Hong Kong and randomly allocated into two groups. All participants will attend the exercise training 3 days per week for 3 months but the mode of delivery will differ, either online as the tele-exercise group (TE) or face-to-face as the community-based group (CB). The outcome measures include muscle strength, physical function, exercise adherence and dropout rate, psychological and social well-being will be assessed at the baseline, and the 3rd, 6th and 12th month. Some participants will be invited to attend focus group interviews to evaluate their overall experience of the tele-exercise training.

**Discussion:**

Tele-exercise reduces the barriers to exercise, such as time constraints, inaccessibility to facilities, and the fear of frail older people leaving their homes. Promoting an online home-based exercise programme for older people can encourage them to engage in regular physical activity and increase their exercise adherence even when remaining at home. The use of telehealth can potentially result in savings in cost and time. The final findings will provide insights on delivering exercise via telehealth to older people and propose an exercise delivery and maintenance model for future practice.

**Trial registration:**

Chinese Clinical Trial Registry (https://www.chictr.org.cn/hvshowprojectEN.html?id=219002&v=1.1), registration number: ChiCTR2200063370. Registered on 5 September 2022.

## Background

The decline of muscle mass and strength with age will expose older people to a higher risk of sarcopenia and falls. Falls are common among older people. The 1-year prevalence of falls among community-living older people aged 65 years or above with at least one fall is 20% with the fall rate (number of falls per 100 people) 29% in Hong Kong [1]. After the age of 75, the fall rates are even higher [2]. Hip fracture is one of the outcomes of falls among older people and is associated with rehospitalization and increases in hospital stay and mortality rates [3, 4]. Sarcopenia is one of the main reasons of disability, falls and hip fractures in older people and it is a challenge in regard to healthy ageing [5]. To reduce the prevalence and incidence of falls and sarcopenia among older people, exercise training is found to have positive effects on balance, muscle mass and strength, as well as physical functioning [6, 7]. Nevertheless, older people are less likely to participate in fall prevention programmes with exercise classes in Hong Kong because frail older people may not be confident to leave their home and join a programme in the community [8]. Thus, it is necessary to find feasible alternatives to encourage and facilitate older people to develop regular exercise habits.

Telehealth refers to the remote delivery of health care services such as clinic appointments and exercise training (tele-exercise), using information and communication technologies (ICT) where the provider and service recipient are in different physical locations [9]. Occupational and physical therapy practitioners increasingly use tele-exercise to enable real-time interactions between instructors and community-dwelling older people in order to save money and waiting time [10, 11]. Promoting an online home-based exercise programme for older people can encourage them to engage in regular physical activity and increase their exercise adherence even when remaining at home. Tele-exercise was particularly important when people needed to adhere to social distancing during the pandemic.

The Otago Exercise Programme (OEP) is an evidence-based fall prevention programme developed in the late 1990s [12, 13]. It consists of five warm-up exercises (head movement, neck movement, back extension, trunk movement and ankle movement) and 17 strength and balance exercises. The original programme was designed as a home-based exercise for older people with guidance and monitoring provided by trained professionals [14]. Many studies have implemented the OEP as an intervention programme for older people to prevent falls and demonstrated positive outcomes, including reduced fall-related injuries and improved functional mobility and balance [15–21]. Similar results were observed in a modified OEP too. The modified formats included additional multisensory balance exercises, augmented reality, training in groups and a DVD delivery format. The OEP in a group is preferable as exercising in a class can offer additional psychological and social benefits [22]. In addition, engagement between the participants and instructors is an essential factor for exercise maintenance, as demonstrated by Davis et al. [23] who delivered the OEP by video along with a single visit by a physical therapist. Compared with studies that involve more participant interaction, the OEP group with less participant interaction resulted in a higher rate of loss to follow-up, with approximately 29.5% of participants failing to complete the post-intervention assessment. Thomas et al. [24] believe that maximizing compliance can improve health outcomes. The OEP is more suitable for older adults who are more prone to falls and less active as the movements required in the exercises are straightforward and of low intensity. However, it lacks interesting variations of movements that may affect compliance [25]. The number of dropouts of OEP modified formats reached 30% [22].

Considering the possible benefits of tele-exercise, as well as the factors that affect exercise compliance and exercise maintenance, we hypothesize that the modified Otago exercise programme delivered via the tele-exercise approach is as effective as traditional exercise programmes among older people at risk of falls. The purposes of this study are to (i) evaluate the effectiveness of tele-exercise on physical functioning and exercise adherence among community-dwelling older people with possible sarcopenia or at risk of falls in comparison with a community-based group, (ii) to evaluate older people’s experience with tele-exercise, with an emphasis on their psychological welfare, social well-being, and acceptance of the telehealth approach.

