### Sample size calculation

In Hong Kong, there are 1,322,000 residents who are aged 65 years or above [29] and it is estimated that 118,980 of them suffer from sarcopenia (prevalence is 9% for those aged 65 or above [30, 31] and 264,400 of them have had at least one fall in the past year [1]. Calculations were performed using G*Power software and an assumed effect size of 0.367 based on a previous study by Benavent-Caballer et al. [32] on the Time Up and Go Test. Considering a 95% confidence level, a power of 80%, and 20% attrition rate (including mortality) [33], a sample size of at least 92 are required.

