### Interventions

All participants will attend the exercise training 3 days per week for 3 months, under the delivery mode of either tele-exercise or a community-based approach. The community-based group will serve as a positive control as the effectiveness of the OEP to prevent falls is well established [24] and the aims of the current study focus on the effectiveness of the new mode of delivery, i.e. tele-exercise. The exercise programme will be structured with a warm-up, Otago strengthening and balance retraining exercises, “workouts on-demand” and cool down (Table 2). The OEP consists of five warm-up exercises (head movement, neck movement, back extension, trunk movement and ankle movement) and 17 strength and balance exercises [14]. For the “workouts on-demand” part, participants will express their needs such as focusing more on the upper body, flexibility, or strength. The instructor will present real-time demonstrations to promote exercise empowerment. Both groups of participants will be divided into classes of 9–10 people. In addition, they will be asked to maintain their daily number of steps at 10,000 or increase their step count by 3,500 compared with their usual habit. They will be required to record all the exercises they perform, the number of steps achieved and the fall incidence during the 12 months.

**Table 2 Tab2:** Lesson plan for both TE and CB groups

Content	Duration
Warm-up (dynamic and static stretching)	~ 10 min
A short pause to allow participants to be ready for the next part and interact with the instructor	
Otago exercise programme-strengthening exercises	~ 10 min
A short pause to allow participants to be ready for the next part and interact with the instructor	
Otago exercise programme- balance retraining exercises	~ 10 min
Workouts on-demand allow participants to - express their opinions on the exercises - request targeted training for specific body parts at a higher or lower level	5–10 min
Cool down	~ 10 min

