### Statistical analysis

Descriptive data of the two groups including age, risk of falls, body mass index, muscle mass, and activity level at the baseline will be analyzed by independent t-test to test the homogeneity of the physical characteristics between the two groups. We will use an intention-to-treat analysis based on all randomized participants following the guidelines on randomized controlled trials [43]. We will perform a sensitivity analysis for missing data. The Kolmogorov-Smirnov one-sample test will confirm the normal distribution of all the measurement variables. A two-way repeated measures ANOVA will be performed for all the outcome measures, accounting for the group (TE and CB) and the interaction term between group and time. The p-value will be set at 0.05 for all tests. All statistical analyses will be carried out using SPSS, version 26.0 (IBM Co., Armonk, NY) by an independent statistician who will not be involved in the outcome assessment. Missing data will be complemented by using the multiple imputation method.

Both groups of participants will also be invited to attend focus group interviews with an experienced qualitative researcher. The Theory Domain Framework will be adopted to examine the determinants of behaviour change [44]. Data analysis will follow a framework approach [45] and use Qualitative Data Analysis (QDA) Miner 5 of Provalis Prosuite, which is qualitative data analysis software.

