## Discussion

This study evaluates whether the tele-exercise approach is comparable to a traditional face-to-face exercise class in terms of physical functioning and exercise adherence during the 3-month intervention and the subsequent 9-month maintenance phase among the older people with possible sarcopenia or at risk of falls. Traditional face-to-face exercise classes allow the instructor to monitor older people’s performance and promote social interaction. However, the time and space available for such group classes for older people are limited. Frail older people may have less confidence to leave their home to attend classes in the community [8]. They may need support from their family. The transportation arrangements may also affect how likely they will participate in the programme. The recent social distancing policy during the COVID-19 pandemic has also been a crucial factor resulting in the frail older people baulking from participation in exercise programmes in the community. Consequently, health professionals are also urging governments to prepare for the next pandemic [46]. Considering older people are more willing to do strength and balance training at home [47], a feasible and effective alternative should be offered to them. The tele-exercise approach in this study uses an online communication application, Zoom, to deliver live group exercise classes in their home. It is convenient in that this approach avoids commuting time and older people can attend classes even in bad weather and could also do so during the pandemic. Frail older people can exercise with others at the same time with less social consciousness and peer pressure [48]. The strength of the current study is that we consider the needs of older people to interact and their fear of new technology. Each lesson will be well structured with a short break every 10 min to allow interaction in both groups. The team will arrange a home visit to the TE group before the intervention period and guide the setting up of the tablet and their home environment such as the angle of the tablet stand, where the tablet and chair should be positioned and where the participant should stand. During the lessons, our team will control the tablet of each participant remotely to minimize any technological problems that they may encounter.

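### The hypothesis claims that tele-exercise matches face-to-face classes, but the plan has only a difference test at 0.05 and no margin, so no result it can produce would support that claim

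*Protocol article*

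**What the plan says.** The protocol article makes a claim of sameness in three places.

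- Background, hypothesis: "we hypothesize that the modified Otago exercise programme delivered via the tele-exercise approach is as effective as traditional exercise programmes".
- Discussion, opening sentence: "This study evaluates whether the tele-exercise approach is comparable to a traditional face-to-face exercise class in terms of physical functioning and exercise adherence".
- Interventions: "The community-based group will serve as a positive control as the effectiveness of the OEP to prevent falls is well established". Both arms follow the same lesson plan (Table 2), and only the mode of delivery differs.

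The design and analysis sections are written for finding a difference.

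- Sample size calculation: "an assumed effect size of 0.367 based on a previous study" on the Timed Up and Go test, with 95% confidence, 80% power and 20% attrition, giving at least 92 participants. The article does not say whether 0.367 is Cohen's d or f, and it does not name the G*Power test.
- Statistical analysis: "A two-way repeated measures ANOVA will be performed for all the outcome measures, accounting for the group (TE and CB) and the interaction term". The interaction meant is group by time. The same section sets the test level: "The p-value will be set at 0.05 for all tests".

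None of these sections gives a non-inferiority or equivalence margin or a rule based on a confidence interval. None says how a non-significant result will be interpreted.

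**The concern.** The null hypothesis of the planned ANOVA is that the two groups do not differ, which is in substance the trial's own hypothesis. A significant result can count against the hypothesis. A non-significant result only fails to reject it, and that becomes more likely with fewer participants, noisier measurement or more dropout. The design therefore gives no way to earn the conclusion that the Background and Discussion set out to reach.

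If tele-exercise were reported as comparable on this basis, services could replace supervised classes on evidence that does not rule out a material loss of function. This cannot simply be left to an unseen analysis plan. The article itself fixes the hypothesis, the basis of the sample size, the test and the recruitment target of 92, and these do not fit together. A margin chosen later could not have been the basis for 92.

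**Working it through.** **Inputs from the article.** Total 92; attrition 20%; effect size 0.367 (metric not stated); ten centres, about ten people each, a similar number of centres per arm; test level 0.05.

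**Inputs assumed here.** Correlation of baseline with outcome r = 0.7; intraclass correlation (ICC) 0 to 0.05; margins in SD units, for illustration only.

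**1. The article's own figure.**
- If 0.367 is d, two-sided: n per arm = 2(1.96 + 0.8416)²/0.367² = 116.6, so 117. The total is 234, and 234/0.8 = 293 with attrition.
- If 0.367 is f with two groups, the total is 62, and 62/0.8 = 78 with attrition (75 if 62 is multiplied by 1.2).
- Neither gives 92. A figure of 92 appears only under settings that do not match the design, for example a multivariate interaction test with three measurement times: 76 × 1.2 = 91.2, so 92. The figure cannot be traced, but this does not show it to be wrong. The points below do not depend on how it was obtained.

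**2. Precision.** Evaluable: 92 × 0.8 = 73.6, about 74, or 37 per arm. The 95% CI half-width for a standardised difference is:
- unadjusted, no clustering: t(0.975, 72) × √(4/74) = 1.993 × 0.2325 = 0.46 SD;
- baseline-adjusted at r = 0.7, no clustering: 0.463 × √(1 − 0.49) = 0.33 SD;
- centre-level, 8 df, 7.36 evaluable per centre, ICC 0: 2.306 × √(4 × (1/7.36)/10) = 0.54 SD;
- the same at ICC 0.05: 2.306 × √(4 × (0.05 + 0.95/7.36)/10) = 0.62 SD.

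**3. Chance that a real deficit goes undetected.** For a true deficit of 0.367 SD, the standardised shift is 0.367 × √(37/2) = 1.579. Power is Φ(1.579 − 1.96) = 0.35, so a simple unadjusted two-group test is non-significant about 65% of the time. For a true deficit of 0.5 SD the figure is about 42%.

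**4. What 92 would give under a non-inferiority rule.** Power = Φ(margin × √(37/2)/√(1 − r²) − 1.96), with true difference zero, one-sided 0.025 and no clustering.

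| Margin (assumed) | r = 0 | r = 0.7 |
|---|---|---|
| 0.367 SD | Φ(−0.38) = 35% | Φ(0.25) = 60% |
| 0.734 SD (if 0.367 is f, d = 2f) | Φ(1.20) = 88% | not computed |

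**5. Size needed for 80% power, unadjusted, no clustering.** Total evaluable / recruited with 20% attrition:
- margin 0.30 SD: 350 / 438;
- margin 0.367 SD: 234 / 293;
- margin 0.50 SD: 126 / 158.

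Baseline adjustment lowers these. At r = 0.7 and 0.367 SD, 116.6 × 0.51 = 59.4, so 60 per arm, 120 evaluable and 150 recruited. Clustering raises them. The unadjusted 293 becomes 425 at an assumed ICC of 0.05.

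The calculations in steps 2 to 4 use simple two-group comparisons, not the planned ANOVA. The planned group-by-time test, with two groups and four times, has (2 − 1)(4 − 1) = 3 numerator degrees of freedom and no direction. It gives no bound on how much worse tele-exercise could be.

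**The case against.** - **The article never says that p > 0.05 will be taken as proof of equivalence.** This is correct. A reader might infer it, but the Statistical analysis section has no rule for interpreting a non-significant result. The documents support only the narrower point that no other planned result could be offered for the hypothesis.
- **The formal objectives are neutral.** The Abstract and purpose (i) speak of evaluating effectiveness in comparison with the community-based group, and the article suggests that tele-exercise may raise adherence. A difference test suits those aims. It would therefore be too strong to infer that the analysis answers none of the trial's questions. The conflict is with the hypothesis and its restatement in the Discussion.
- **A trivial but significant difference might refute the hypothesis.** A reader might fear this too, but the precision above makes it unlikely. An unadjusted difference would have to reach about 0.46 SD to be significant, and more in a centre-level analysis.
- **The comparison with 0.367 depends on what that figure is.** This stands. If it is f, the matching difference is 0.734 SD and every half-width above is below it. Even if it is d, the adjusted half-width without clustering (0.33 SD) is slightly smaller. It cannot be said without qualification that the interval is wider than the design effect. What survives every reading is that neither value is presented or justified as a margin.
- **A well-powered non-inferiority trial would not be cheap.** This also stands, and it is why rewording comes first in the fix.

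**Conclusion.** The point holds as a mismatch inside the article: a claim of equal effectiveness against a positive control, a sample size built on an effect size, and a difference test with no margin. The planned analysis can count against the hypothesis but cannot support it. This conclusion needs no assumed figure.

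Its practical size does rest on assumptions. Half-widths run from about 0.33 SD (r = 0.7, no clustering) to about 0.62 SD (unadjusted, centre-level, ICC 0.05). Non-inferiority power for an illustrative 0.367 SD margin is 35% to 60% before clustering. The 88% figure applies only to a 0.734 SD margin that the article neither states nor justifies. The case does not require 92 to be wrong, and the working does not show that it is.

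**What to change.** Choose one of two routes.

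(a) **Reword.** Drop the equal-effectiveness hypothesis and state the aim as estimating the difference between tele-exercise and community-based delivery. Report it with a 95% CI that respects allocation by centre. State that p > 0.05 will not be taken as comparability.

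(b) **Keep the claim and test it.** Fix and justify a non-inferiority margin on a primary outcome and time point of the sponsor's choosing. Timed Up and Go, already used for sizing, is the natural candidate, but the choice is the sponsor's. Conclude non-inferiority only if the CI excludes the margin, and restate the power that 92 gives for it.

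The margin should be set before outcome comparisons are seen. Trial Status reports two community-based groups past the 3-month intervention, both tele-exercise groups still in it, and five groups still to be recruited. At that date no 3-month comparison between arms was yet possible.

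Route (a) costs wording only. Route (b) costs a justified margin and an honest power statement, and reaching 80% power could require many more participants. Under either route the trial may have to report an inconclusive result where it hoped to report comparability.

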## Methods/design

 This is a 3-month single-blind, randomized controlled trial (RCT) with subsequent 9 -month follow-up comparing online (TE) with face-to-face exercise training (CB) for community-dwelling older people at risk of falls. The design and conduct of the study follows the requirements of the Standard Protocol items: Recommendations for Interventional Trials (SPIRIT) checklist [26], as shown in the flow chart of the study in Fig. 1. The protocol reported is based on the SPIRIT 2013 statement [26] (Fig. 2). The participants will be recruited from elderly community centres in Hong Kong. To facilitate the recruitment of participants, health talks about fall prevention and maintaining muscle mass will be arranged at local community centres. The potential participants will be screened and assessed through on-site enquiries and video interviews.

**Fig. 1 Fig1:**
[figure not shown]
Flow chart of the study

**Fig. 2 Fig2:**
[figure not shown]
Schedule of enrollment, interventions, and assessments based on SPIRIT2013 statement [26]

